#### Exclusion criteria

In all phases, patients will be excluded from the study when admitted to the MHB ASU outside of business hours (i.e., outside of 0800 h – 1630 h weekdays, weekends, or public holidays) when allied health services are not fully staffed; when allied health assessment has already been completed during the admission; if a third-party professional interpreter is unavailable for patients from non-English speaking backgrounds; and/or if the patient has been included in the study previously.

### Processes

#### Recruitment and consent

The study procedure for participants and staff is outlined in Fig. 2. Across all Phases, on day 1 of admission to the MHB ASU, patient participants will be recruited using convenience sampling (i.e., as they are admitted). To identify participants who meet the eligibility criteria, the physiotherapists and/or occupational therapists will review the admitting doctor note in the patient medical record. Participants will be provided with a Participant Information and Consent Form and will provide written consent if agreeing to take part in the study (see Additional file 2). Where it is not possible to obtain written consent due to quick discharge from hospital (i.e., before day 2 on the acute stroke unit when consent is obtained), verbal consent will be obtained via phone call, as approved by the ethics committee. On day 2 of admission, eligible patient participants will be asked to partake in a satisfaction survey. At 3-months after admission to hospital eligible participants (and/or authorised representatives) will receive a follow-up phone call to measure functional outcomes and quality of life.

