## Background

Allied health professionals (AHPs) are central to the provision of quality stroke services. The Australian stroke guidelines state that all people experiencing stroke should receive physiotherapist assessment within 24–48 hours of admission to hospital, and assessment by occupational therapists and speech pathologists within 48 hours of admission [1]. While each AHP has a clearly defined role, overlapping skills and knowledge result in some assessment tasks and questions being administered repeatedly by different clinicians [2–4]. At the Mater Hospital Brisbane (MHB) Acute Stroke Unit (ASU), the physiotherapist, occupational therapist, and speech pathologist assess patients presenting with stroke separately. However, these discipline-specific assessments overlap, for example the physiotherapist and occupational therapist both assess upper limb function and gather information on previous level of function and the home environment. Such duplication across allied health assessments is unnecessary, inefficient, and AHP time could be better utilised.

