A transdisciplinary approach to allied health stroke assessment could streamline AHP services, which is pertinent given the increasing consumer demand for stroke care. In Australia, the number of new stroke diagnoses per year is predicted to grow from 27,000 in 2020 to exceed 50,000 by 2050 [5]. Transdisciplinary approaches are defined by their potential to build workforce capacity by blurring lines of traditional responsibilities and integrating aspects of care (such as assessment) to enable a single team member to deliver the occasion of service [6–9]. There is emerging evidence that demonstrates, when compared to usual care, hospital-based allied health transdisciplinary teams improve AHP time-efficiency, quality of care, and are cost-effective [3, 10, 11]. No negative or harmful outcomes were reported [3, 10, 11]. When pilot testing the allied health transdisciplinary assessment to be used in this study, the authors demonstrated a mean time saving of 103 minutes when the transdisciplinary assessment was used (42 minutes), compared to usual single-dicipline assessments (145 minutes) [12]. A time saving of 103 minutes could be clinically significant. For example, AHPs would have more time available to commence rehabilitation earlier in the patient episode of care, thereby aligning the service more closely with national stroke guidelines [1]. The pilot testing served as proof of concept for the study proposed in this paper. To the author’s knowledge, no other empirical studies have evaluated transdisciplinary approaches on ASUs. Due to the low volume of empirical evidence pertaining to transdisciplinary approaches on ASUs, alongside the potential for transdisciplinary approaches to streamline stroke services, empirical research is warranted in this field.

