**Fig. 2 Fig2:**
[figure not shown]
Recruitment timeline for patients and staff

Staff working on the MHB ASU will be provided with a Healthcare Provider Information and Consent Form before agreeing and completing the satisfaction and interprofessional trust surveys (see Additional file 3). The surveys will remain open for 5 business days and returned to a secure slot box or submitted online. Staff will be invited to participate in a focus group at the end of Phase 4. The ASU occupational therapists, physiotherapists, speech pathologists and social workers will be invited to complete a series of online staff confidence surveys before/after completing competency training and at monthly intervals during the implementation Phases 2 and 4. Patients and staff may decline to consent or withdraw their consent to participate at any point and for any reason without prejudice. Upon withdrawal no further data will be collected.

#### Baseline phases 1 and 3

For statistical purposes, the baseline data will be gleaned from Phases 1 and 3 where discipline-specific allied health stroke assessments are utilised within 48 hours for patients admitting to the MHB ASU (i.e., the existing physiotherapy, occupational therapy, and speech pathology stroke assessment).

#### Implementation phases 2 and 4

The novel TINSA (see Additional file 4) replaces discipline-specific allied health stroke assessments and will be utilised within 48 hours of admission to the MHB ASU in Phases 2 and 4. The novel TINSA has been developed in full collaboration with the health professionals on the MHB ASU, including occupational therapy, physiotherapy, speech pathology, social work, nursing staff, and the stroke clinical nurse consultant. The TINSA includes sections on social history, mood, previous level of function, home environment, communication, swallow, respiratory function, vision, cognition, upper limb function, lower limb function, and mobility. Due to the content and clinical skills required, the TINSA can be administered by trained physiotherapists or occupational therapists. The novel TINSA was approved and published in the hospital Policy and Procedure Library prior to use in the study.

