#### Staff and patient satisfaction surveys

The patient satisfaction survey asks participants to recall their experience of allied health assessment the previous day (see Additional file 5). The survey will be completed in written form if the patient remains in hospital, or via phone call if the patient has discharged from hospital. A paper-based staff satisfaction survey will ask MHB ASU staff to reflect on their experience of the TINSA (see Additional file 6). Both satisfaction surveys will utilise open-ended and multiple-choice questions.

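### The patient satisfaction survey is tied to day 2 of admission and not to completion of the assessment, so usual care is more likely than the TINSA to be rated while incomplete

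*Protocol article*

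**What the plan says.** Three statements in the protocol article bear on this point.

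- **When the survey is given.** Recruitment and consent: "On day 2 of admission, eligible patient participants will be asked to partake in a satisfaction survey".
- **What it asks.** Staff and patient satisfaction surveys: the survey "asks participants to recall their experience of allied health assessment the previous day". It is done on paper in hospital, "or via phone call if the patient has discharged from hospital".
- **When the assessment may take place.** Under Baseline phases 1 and 3, "discipline-specific allied health stroke assessments are utilised within 48 hours for patients admitting to the MHB ASU". Under Implementation phases 2 and 4, the TINSA "will be utilised within 48 hours of admission to the MHB ASU in Phases 2 and 4".

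The Background describes usual care as several contacts: "the physiotherapist, occupational therapist, and speech pathologist assess patients presenting with stroke separately". The TINSA replaces these with one assessment by a trained physiotherapist or occupational therapist. The Inclusion criteria ask for the survey only in Phases 1 and 2, from patients scoring at least 19/30 on the MoCA, so the comparison affected is Phase 1 v Phase 2.

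**The concern.** The survey follows the calendar of the admission, whereas the thing being rated can happen later. If the previous day is day 1, an assessment on day 2 or later is not covered, although the protocol allows it. A patient with only part of the assessment done on day 1 rates that part. A patient with none done on day 1 has nothing to recall.

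This would be mere noise if it struck both phases equally. It may not. Three separate contacts are more likely to spill past day 1 than one, so the two phases may be rating different fractions of their assessment. Patient satisfaction is a stated secondary aim and a listed outcome. The rationale for the TINSA is duplication between disciplines, which a patient meets only once a second clinician has called. If later contacts drop out of the rating, usual care may look better than it was. A larger sample would not correct that.

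**Working it through.** **Setting the statements side by side.** The survey is on day 2 and its recall period is the day before, hence day 1. The permitted assessment window is 48 hours. For a patient admitted between 0800 and 1630 on day 1, that window closes between 0800 and 1630 on day 3 (counting calendar days). All of day 2 and part of day 3 therefore lie inside the assessment window and outside the recall period. This step needs no assumption about workload and applies to both phases.

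**Does the difference between phases have a plausible size?** The article gives no figure for how often assessment runs past day 1, so there is none to reproduce. The following is an illustration.

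Inputs:
- Admission hours for inclusion, 0800 to 1630 (Exclusion criteria): 8.5 × 60 = 510 minutes.
- Pilot mean times (Background): TINSA 42 minutes, usual care 145 minutes. The difference, 145 − 42 = 103 minutes, agrees with the saving that the article reports.
- Range for usual care (Statistical power): 80 to 210 minutes.

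Assumptions, none of which is in the article: arrivals are uniform over the 510 minutes, assessments follow one another, nothing is done after 1630 on day 1, and all recorded time counts as elapsed time.

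Formula: share unable to finish on day 1 = (assessment time + delay before the first assessment) / 510.

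| Delay (assumed) | TINSA, 42 min | Usual care, 80 min | Usual care, 145 min | Usual care, 210 min |
|---|---|---|---|---|
| 0 min | 42/510 = 8% | 80/510 = 16% | 145/510 = 28% | 210/510 = 41% |
| 60 min | 102/510 = 20% | 140/510 = 27% | 205/510 = 40% | 270/510 = 53% |
| 120 min | 162/510 = 32% | 200/510 = 39% | 265/510 = 52% | 330/510 = 65% |

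At the pilot means the gap between phases is 103/510 = 20 percentage points, whatever the common delay.

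**How far this can be trusted.** The article's definition of assessment time includes reading the record and documenting results, which need not involve the patient and can overlap between clinicians. If patient contact were half of the recorded time (an assumption; the share is not given), the shares without delay would be 72.5/510 = 14% and 21/510 = 4%, a gap of 10 points. Clinicians working at the same time would also lower the usual-care share. Waiting, and fitting three disciplines into one afternoon, would raise it. The percentages are therefore neither a lower nor an upper bound.

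**The case against.** The strongest reply is that the two survey statements agree with each other if day 1 is the usual day of assessment. On that reading 48 hours is the guideline ceiling and not the typical time, and most patients are surveyed the day after a completed assessment. The recruitment timeline (Fig. 2) and the survey itself (Additional file 5) are not shown and may say more. This is a fair account of the likely intention, but nothing in the text shown links the survey to completion, and the telephone route covers only patients who have gone home.

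Three stronger readings are tempting, and the article does not support them.

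- *Usual care often cannot be finished on day 1.* No frequency is given. Even in the illustration without delay, 72% of usual-care arrivals could finish at the pilot mean (100 − 28).
- *An incomplete usual care is compared with a complete TINSA.* The TINSA has the same 48-hour window, and some TINSA assessments would be missed as well.
- *A first contact on day 2 is commoner under usual care because it takes more staff time.* Total staff time does not determine when the first clinician arrives. Any of three disciplines can make the first contact under usual care, but only a trained physiotherapist or occupational therapist can under the TINSA.

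The direction of bias is also open to challenge. The article's example of duplication is between physiotherapy and occupational therapy. A patient seen by both on day 1 has met the repetition even if speech pathology follows later.

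Finally, a fixed survey day keeps timing equal between phases, and moving it gives that up. That is a real trade-off but a small one: equal timing is of little use if the thing rated is unequally complete.

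**Conclusion.** The point holds in a limited form. Day-2 administration, recall of the previous day and a 48-hour assessment window do not fit together, and compliant assessments can go unrated in either phase. Because usual care is three assessments and the TINSA one, incomplete rating is more likely in Phase 1, and the satisfaction comparison may be biased.

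The size is unknown. The illustrative 28% (16% to 41%) v 8% depends on uniform arrivals, sequential work, a stop at 1630 and staff time standing in for elapsed time. A bias in favour of usual care is plausible but not established. Satisfaction is a secondary outcome, and neither the primary outcome nor the sample size of 26 per group is affected. The change is worth making because it is cheap.

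**What to change.** In both phases:

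1. Give the survey on the day after the last initial assessment, meaning the TINSA or the last of the three discipline assessments.
2. Word the recall as *your initial allied health assessment(s)* instead of the previous day.
3. Use the existing telephone route for patients already discharged.
4. Record the day and mode of each survey, so that any difference between phases can be described.

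If surveys have already been taken under the current rule, the times from admission to each discipline's assessment, which Table 1 already lists, would help to describe how many patients were surveyed before their assessment was finished.

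The cost is a change to one line of timing and to the survey wording. Some Phase 1 surveys come a day later and more are done by telephone, so survey time and mode may differ somewhat between phases; item 4 is there for that reason. No extra patients or staff are needed.

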**Fig. 2 Fig2:**
[figure not shown]
Recruitment timeline for patients and staff

Staff working on the MHB ASU will be provided with a Healthcare Provider Information and Consent Form before agreeing and completing the satisfaction and interprofessional trust surveys (see Additional file 3). The surveys will remain open for 5 business days and returned to a secure slot box or submitted online. Staff will be invited to participate in a focus group at the end of Phase 4. The ASU occupational therapists, physiotherapists, speech pathologists and social workers will be invited to complete a series of online staff confidence surveys before/after completing competency training and at monthly intervals during the implementation Phases 2 and 4. Patients and staff may decline to consent or withdraw their consent to participate at any point and for any reason without prejudice. Upon withdrawal no further data will be collected.

#### Baseline phases 1 and 3

For statistical purposes, the baseline data will be gleaned from Phases 1 and 3 where discipline-specific allied health stroke assessments are utilised within 48 hours for patients admitting to the MHB ASU (i.e., the existing physiotherapy, occupational therapy, and speech pathology stroke assessment).

#### Implementation phases 2 and 4

The novel TINSA (see Additional file 4) replaces discipline-specific allied health stroke assessments and will be utilised within 48 hours of admission to the MHB ASU in Phases 2 and 4. The novel TINSA has been developed in full collaboration with the health professionals on the MHB ASU, including occupational therapy, physiotherapy, speech pathology, social work, nursing staff, and the stroke clinical nurse consultant. The TINSA includes sections on social history, mood, previous level of function, home environment, communication, swallow, respiratory function, vision, cognition, upper limb function, lower limb function, and mobility. Due to the content and clinical skills required, the TINSA can be administered by trained physiotherapists or occupational therapists. The novel TINSA was approved and published in the hospital Policy and Procedure Library prior to use in the study.

Alongside the TINSA, a competency training package has been developed to foster new skill attainment, standardise assessment administration, and support safe implementation of the novel TINSA. The training package consists of four components: 1) a comprehensive manual, 2) quick reference guide, 3) nine eLearning Modules, and 4) a competency assessment. The nine eLearning Modules and competency assessment are mandatory components of the training package, providing targeted learning on topics which were identified as being beyond the usual scope of practice for a new graduate and/or experienced physiotherapists or occupational therapists. [name] and colleagues describe the development of the TINSA and training package in more detail [12].

### Outcome measures

A complete list of outcome measures is provided in Table 1.

**Table 1 Tab1:** List of outcome measures

Outcome	Measures
Time-efficiency	• Total time of allied health stroke assessments • Time from admission to enactment of social work referral • Time from admission to commencement of allied health intervention/rehabilitation • Occasions of face-to-face service with AHPs (occupational therapy, physiotherapy, speech pathology, social work) • Number of referrals to AHPs (occupational therapy, physiotherapy, speech pathology, social work) where no intervention or further assessment is indicated • Number of patients who received allied health assessment but had a negative stroke diagnosis on MRI • Time from admission to discharge from allied health (occupational therapy, physiotherapy, speech pathology) • Length of hospital stay
Cost savings	• Economic evaluation to determine difference in utilisation of hospital resources, such as bed space and AHP time
Quality of care (patient safety)	• Total number of adverse events during the hospital admission that may be related to allied health input (falls, extension of stroke, aspiration pneumonia, pressure injuries) • Missed allied health referrals (other than those due to a change in condition) • Failed discharge, defined as unplanned readmission within 30 days not related to a new episode of care
Quality of care (compliance to national stroke guidelines)	• Time from admission to allied health assessment (occupational therapy, physiotherapy, speech pathology) • Time from admission to commencement of allied health intervention (occupational therapy, physiotherapy, speech pathology) • Time from admission to mobility assessment • Time from admission to communication assessment
Utility of the novel TINSA	• Number of sections attempted/completed on the novel TINSA • Number of “stop and refer” prompts used on the novel TINSA • Number of allied health referrals identified from the novel TINSA
Patient and staff satisfaction	• Patient satisfaction survey • Staff satisfaction survey • Staff focus group
Staff trust and confidence	• Staff interprofessional trust surveys • Staff confidence surveys (pre/post competency training) • Staff building confidence surveys (monthly intervals)
Patient outcomes at 3-months from hospital admission	• EQ-5D-3L as a measure of quality of life • Modified Rankin Scale (MRS) as a measure of disability • Health event questions pertaining to community falls, hospital readmissions, help from family/friends, formal support services.

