#### Quantitative data analysis

For each participant group, two periods of time to measure standard discipline-specific allied health assessment and the TINSA assessment will be evaluated and compared. Patient characteristics, outcomes and quantitative survey responses will be summarised for each assessment group using frequency and percent for categorical variables, means and standard deviations for approximately normally distributed continuous variables, and medians and interquartile ranges for non-normally distributed continuous variables. Differences between assessment groups will be estimated using the general linear model for continuous outcomes and logistic regression for categorical outcomes. Balance of potential confounders between the assessment groups will be investigated and multivariable adjustment will be employed where there is an apparent confounding effect. Results will be presented as differences (continuous outcomes) and odds ratios (categorical outcomes) with 95% confidence intervals. All analyses will be performed using Stata 15.1 (Stata Corp, College Station, TX) and a *p*-value < 0.05 will be considered statistically significant throughout all inferential analysis.

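### Times to social work referral and to start of allied health intervention exist only for patients who have the event, so a linear-model difference in these secondary outcomes is biased if that share differs between phases.

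*Protocol article*

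**What the plan says.** Under time-efficiency, Table 1 (Outcome measures) lists "Time from admission to enactment of social work referral" and "Time from admission to commencement of allied health intervention/rehabilitation". Time to commencement of intervention appears again under compliance with the national guidelines, by discipline. These are two of the eight time-efficiency measures and one of the four compliance measures. The primary outcome, total assessment time, is separate.

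For the comparison of phases, the Quantitative data analysis section states: "Differences between assessment groups will be estimated using the general linear model for continuous outcomes and logistic regression for categorical outcomes". It continues: "Results will be presented as differences (continuous outcomes) and odds ratios (categorical outcomes) with 95% confidence intervals". On adjustment it says that "multivariable adjustment will be employed where there is an apparent confounding effect". Medians are mentioned only for descriptive summaries of skewed variables. The article names no time-to-event method.

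**The concern.** A time from admission to an event has no value for a patient in whom the event never happens, and the article itself expects such patients:

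- Inclusion criteria: Phases 1 and 2 take TIA and symptoms that have already resolved.
- Table 1: referrals are counted "where no intervention or further assessment is indicated", as are missed referrals.
- Recruitment and consent: provision is made for patients discharged before day 2.

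A linear model fitted to these times therefore works on a subset defined after the assessment. The assessment is what changes between phases. The TINSA replaces the three discipline-specific assessments, is given by a physiotherapist or occupational therapist, and covers social history, mood and home environment. Table 1 counts its stop-and-refer prompts and the referrals it identifies. It can plausibly change who is referred or treated, so the two phases may contribute differently selected patients. Adjusting for baseline characteristics that look unbalanced between the full groups does not in general undo that selection.

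At stake is the reading of these two outcomes. The Background gives earlier rehabilitation as an example of why a time saving would matter, and time to intervention is the measure closest to that benefit.

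**Working it through.** **The plan's own figure.** The only sample-size figure is 26 per group for total assessment time (Statistical power: difference 20 min, SD 25 min, alpha 0.05, taken here as two-sided, power 80%). The normal approximation gives n = 2 × (1.96 + 0.84)² × 25² / 20² = 24.5, so 25; the t-test version gives 25.5, so 26. The figure reproduces, and this point does not touch it. The article gives no referral or intervention rates and no time distribution, so every rate and time below is an assumption.

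**Illustration.** Usual care refers 30% of patients at a mean of 20 h. The TINSA refers the same 30% at a mean of 15 h and a further 20% at a mean of 40 h.

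- Mean among those referred, usual care: 20 h.
- Mean among those referred, TINSA: (0.30 × 15 + 0.20 × 40) / 0.50 = 12.5 / 0.50 = 25 h.
- Event-only difference: +5 h, against the TINSA.

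Now count all patients, with exponential times within each subgroup:

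- Referred by 48 h, usual care: 0.30 × (1 − e^(−48/20)) = 0.30 × (1 − e^(−2.4)) = 0.27.
- Referred by 48 h, TINSA: 0.30 × (1 − e^(−3.2)) + 0.20 × (1 − e^(−1.2)) = 0.29 + 0.14 = 0.43.

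The all-patient comparison favours the TINSA (43% v 27%) while the event-only mean goes against it.

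**Dependence on the gap in shares.** Suppose 30% of patients are high-need (always referred, mean 24 h), 30% are mid-need (mean 40 h, referred with probability p) and 40% are never referred. The mean among those referred, before any gain in speed, is

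M(p) = (0.30 × 24 + 0.30p × 40) / (0.30 + 0.30p) = (24 + 40p) / (1 + p).

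If the TINSA makes every referral g hours sooner, the event-only difference is M(p under TINSA) − M(p under usual care) − g. An unbiased result would be −g.

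| Mid-need referred, usual care v TINSA | Share of all patients with a time | M, usual care → TINSA (h) | g = 2 | g = 4 | g = 6 |
|---|---|---|---|---|---|
| 50% v 50% | 45% v 45% | 29.3 → 29.3 | −2.0 | −4.0 | −6.0 |
| 30% v 50% | 39% v 45% | 27.7 → 29.3 | −0.4 | −2.4 | −4.4 |
| 20% v 80% | 36% v 54% | 26.7 → 31.1 | +2.4 | +0.4 | −1.6 |
| 0% v 50% | 30% v 45% | 24.0 → 29.3 | +3.3 | +1.3 | −0.7 |
| 0% v 100% | 30% v 60% | 24.0 → 32.0 | +6.0 | +4.0 | +2.0 |

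A simulation of this set-up agreed to within 0.1 h. With equal shares the true gain is recovered. A gap of 39% v 45% takes about 1.6 h off the gain and keeps its sign. Wider gaps can turn a gain into an apparent loss; whether they do depends on how much later the added patients are, relative to the true gain.

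**Numbers behind the estimate.** With 26 per group, these scenarios leave 26 × 0.30 = 7.8 to 26 × 0.60 = 15.6, so about 8 to 16 patients per group with a time.

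**The case against.** The strongest reply is that the article is a condensed document and its model statement is one generic sentence. It does not assign a model to each Table 1 measure, and a fuller analysis plan could set a rule for patients without the event. That is fair. A reader might infer that the protocol says such patients are dropped. It does not; the exclusion follows from fitting a linear model to a time that does not exist for them. What stands is that the method the text does name, used as written, does not suit these two outcomes.

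Second, the Retrospective medical record audit section gives completion of assessment within 48 hours as its compliance example, which is a proportion. That shows a listed time need not be analysed as mean hours. The example concerns assessment, however, not referral or intervention.

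Third, Table 1 also counts missed referrals, referrals needing no intervention, and occasions of service. A large shift in who is referred should show there. These counts would warn a careful reader, but they do not correct the time estimate.

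Fourth, the effect of the TINSA on referral is not established. The content of its prompts sits in an additional file that is not shown, so a change in who is referred to social work is plausible, not demonstrated. In Phases 3 and 4, if most patients start intervention (no rate is given), the problem for that outcome is small and lies mainly in Phases 1 and 2.

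**Conclusion.** The point holds for two secondary outcomes. A linear-model difference in time to social work referral or to start of intervention compares patients selected after assessment, and it is biased if the share with the event differs between the phases compared. In the assumed scenarios the effect runs from none (equal shares and case-mix), through dilution (a 4 h gain shown as 2.4 h at 39% v 45%), to reversal (a 4 h gain shown as a 1.3 h loss at 30% v 45%). The true size is unknown because the article gives no rates.

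A reader might infer that the trial's main result could be reversed, or that all the time-efficiency and compliance outcomes are compromised. The article supports neither reading. Total assessment time and its sample size are unaffected, and the other listed measures are outside this point.

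**What to change.** For these two outcomes, analyse all participants within each severity group (Phase 1 v 2, Phase 3 v 4):

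- Compare the proportion with the event by a fixed time from admission, chosen in advance (48 h, for example), using the logistic regression already planned.
- Support this with cumulative incidence from admission, treating discharge or death without the event as a competing event.
- Report the proportion ever having the event, by phase.
- Show mean or median time among those with the event as descriptive only.

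The cost is a change of analysis wording. The admission, event and discharge times are already needed for outcomes in Table 1. The downside is some loss of information from dichotomising, and few events: in the illustration, 26 × 0.27 = 7 against 26 × 0.43 = 11 per group. Intervals will be wide and there is little room for covariate adjustment.

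### Hour and weekday of arrival should be pre-set covariates for the secondary time-from-admission outcomes, because the stated rule of adjusting only for apparent confounding can leave their variance in the residual

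*Protocol article*

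**What the plan says.** Table 1 (Outcome measures) lists among the time-efficiency outcomes "Time from admission to enactment of social work referral", "Time from admission to commencement of allied health intervention/rehabilitation" and time to discharge from allied health. Under compliance with national guidelines it lists times from admission to allied health, mobility and communication assessment, and time to start of intervention a second time. No staffed-hours rule is attached to any of them.

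The Exclusion criteria state that "patients will be excluded from the study when admitted to the MHB ASU outside of business hours", defined as outside 0800–1630 on weekdays, weekends and public holidays, "when allied health services are not fully staffed".

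Quantitative data analysis states: "Differences between assessment groups will be estimated using the general linear model for continuous outcomes". On covariates, balance of potential confounders is to be examined and "multivariable adjustment will be employed where there is an apparent confounding effect".

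**The concern.** The exclusion limits when patients arrive, not when later events happen. If an event slips from one afternoon to the next morning, elapsed time picks up the night; if it slips past Friday afternoon, it can pick up the weekend. How likely that is depends on the hour and weekday of arrival. Both are fixed before any assessment and cannot be affected by the TINSA, so they are prognostic and safe to adjust for.

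The stated covariate rule responds to imbalance. When two phases have similar arrival patterns, it gives no reason to include arrival time, and the variance that arrival time explains stays in the error term. The Background argues that time saved on assessment would let rehabilitation start earlier. Time to start of intervention is the outcome that tests this, and an imprecise null result could be read as no service gain.

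**Working it through.** **The plan's own figure.** With a difference of 20 min, SD 25 min, two-sided α = 0.05 (sidedness assumed) and 80% power, n = 2(1.960 + 0.842)² × 25²/20² = 24.5, so 25 per group by the normal approximation. The t-based solution is 25.5, so 26, as stated. This applies to total assessment time only; the article gives no SD, effect or power for the time-from-admission outcomes.

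**Size of the gaps.** From 1630 to 0800 is 24 − 8.5 = 15.5 h. From Friday 1630 to Monday 0800 is 7.5 + 48 + 8 = 63.5 h. These are upper limits, reached only if there is no off-hours service.

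**Simulation inputs, all assumed.** There are 26 patients per phase, with arrivals uniform over 0800–1630 Monday to Friday and the clock starting at admission to the unit. Usual-care wait is gamma (shape 2) with mean 3, 6 or 10 weekday service hours. The TINSA shortens it by 40%. There is no night service, and weekend daytime service is at 0, 25 or 50% of the weekday rate. Tests are two-sided at 5%. The adjusted model adds hour, Friday and hour × Friday. Power in a check with 2,000 trials per cell:

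| Weekend rate | Mean wait (h) | Unadjusted | Adjusted |
|---|---|---|---|
| 0 | 3 | 21% | 30% |
| 0 | 6 | 32% | 47% |
| 0 | 10 | 44% | 55% |
| 25% | 3 | 28% | 39% |
| 25% | 6 | 45% | 53% |
| 25% | 10 | 54% | 61% |
| 50% | 3 | 34% | 42% |
| 50% | 6 | 51% | 58% |
| 50% | 10 | 61% | 62% |

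The gain is about 2 to 15 points. Repeat runs differ by a point or two, so the ranges are about 20–61% unadjusted and 30–63% adjusted. With no true effect, rejection stays near 5% for both models.

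**Different inputs.** This check uses lognormal waits with a coefficient of variation of 0.5, and adjusts for all weekdays, hour and Friday × hour. Partial service means nights at 25% and weekend business hours at 50% of the weekday rate.

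| Mean wait, gain (h) | No off-hours service: unadjusted → adjusted | Partial service: unadjusted → adjusted |
|---|---|---|
| 4, 1.72 | 0.30 → 0.52 | 0.83 → 0.87 |
| 8.5, 1.72 | 0.16 → 0.22 | 0.30 → 0.30 |
| 8.5, 4 | 0.66 → 0.87 | 0.98 → 0.98 |

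The 1.72 h gain is the pilot saving of 103 min (103/60), used only as an illustration. With no off-hours service, arrival hour and weekday explain about 32–57% of the variance of elapsed time for mean waits of 2 to 12 h.

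**Chance imbalance.** With one fifth of arrivals on Fridays, two phases of 26 differ by four or more Friday arrivals with probability 0.22. If all four waited through the weekend, the extra gap per patient would be 63.5 − 15.5 = 48 h, and a phase mean would shift by up to 4/26 × 48 = 7.4 h.

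**The case against.** A reader might infer that night and weekend hours add large noise and that real gains are likely to be missed. The documents do not support that. They say only that allied health is not fully staffed off-hours, which is not the same as no service, and they give neither the usual wait nor an expected gain. Across the lognormal scenarios unadjusted power runs from 0.15 to 0.98, and in some adjustment changes nothing. This part of the objection stands.

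A reader might also infer that the outcomes should be moved to staffed hours. That would change the question. The guideline that patients "should receive physiotherapist assessment within 24–48 hours of admission to hospital" runs on elapsed hours. If some weekend service exists, a patient who arrives on Friday at 1600 scores 0.5 staffed hours whether first treated on Saturday at 1000 or on Monday at 0800, which erases a real 46 h difference. The power advantage of staffed hours is also partly built in when the effect is simulated on that scale. With some night service, three scenarios gave 51%, 62% and 65% on elapsed time against 53%, 53% and 55% on staffed hours.

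Three further objections stand in part:
- Chance imbalance in Friday arrivals is largely covered, because the plan will examine balance and adjust where confounding is apparent. What remains is the precision argument for phases that look balanced.
- Only secondary outcomes without their own power calculation are affected, and the exclusion already removes out-of-hours arrivals at the unit.
- A separate analysis plan may name covariates. But the article does state a covariate rule, and that rule responds to imbalance, not to prognostic value.

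**Conclusion.** The point holds as a cheap improvement of minor severity. On the stated rule, a prognostic factor known before assessment can stay out of the model for the time-from-admission outcomes. Pre-set adjustment raises power by about 2 to 15 points under the no-night-service assumptions. It gives almost nothing when off-hours service is substantial, and in no scenario did it cost more than about one point. These sizes rest on assumed waits, gains and staffing and should not be quoted as the trial's actual loss. Table 1 does not say whether the clock starts at admission to hospital or to the unit; if to hospital, off-hours time before transfer could also count. The primary outcome is timed directly in minutes and is untouched.

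**What to change.** Add one sentence to Quantitative data analysis: for every continuous time-from-admission outcome, the general linear model will include hour of admission, a Friday indicator and their interaction, whether or not the phases appear imbalanced. Build these terms from the admission time that starts the clock, and say which admission that is. Keep elapsed hours as the outcome scale. For the time-efficiency outcomes, staffed hours elapsed may be reported alongside as a supplementary measure, not as a replacement.

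The cost is three degrees of freedom: with 26 per phase, residual degrees of freedom fall from 52 − 2 = 50 to 52 − 5 = 47. The admission time is already needed to apply the business-hours exclusion and to form these outcomes, so the adjustment needs no new data.
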